# **1. INTRODUCTION**

People with mobility limitation can benefit from rehabilitation programs, particularly rehabilitation programs that contain intensive repetitive exercises. New technologies potentially provide an affordable way to increase the dose of exercise and overall physical activity for people in rehabilitation. Exercise-based video and computer games/exercises and activity monitors are increasingly being used in rehabilitation settings to provide feedback on motor performance and physical activity. A randomised feasibility study conducted by our team has demonstrated that a tailored approach to delivering task specific repetitive exercise using a suite of technologies appears promising. However, it requires rigorous evaluation with an adequately powered randomised controlled trial. Therefore, this trial aims to evaluate the effect of the addition of affordable technology to usual care on physical activity and mobility.

The primary research question is:

What is the effect of the addition of affordable technology to usual care on physical activity and mobility 6 months after randomisation in people with mobility limitations admitted to inpatient aged and neurological rehabilitation units compared to usual care alone?

Secondary research questions are:

1. What is the effect of the addition of affordable technology to usual care on physical activity levels and mobility 3 weeks after randomisation in people with mobility limitations admitted to inpatient aged and neurological rehabilitation units compared to usual care alone?

2. What is the effect of the addition of affordable technology to usual care on cognition (3 weeks and 6 months after randomisation), self-reported physical activity, activity performance and participation, utility based quality of life, balance confidence, technology self-efficacy (3 and 12 weeks and 6 months after randomisation) and falls (over the 6-month period after randomisation) in people with mobility limitations admitted to inpatient aged and neurological rehabilitation units compared to usual care alone?

3. How do participants randomised to the intervention group report the usability and enjoyment of technologies prescribed in this trial at 3 and 12 weeks and 6 months after randomisation?

Other research questions (not covered as part of the SAP) are:

1. What is the cost-effectiveness of the intervention compared to usual care over the 6-month period after randomisation?

2. What factors predict greater use of technology for participants randomised to the intervention group over the 6-month period after randomisation?

3. What are the experiences of participants and staff using affordable technology for physical rehabilitation?

The study was approved by the Southern Adelaide Clinical Human Research Ethics Committee, Adelaide, Australia (study number 529.13) and the South Western Sydney Local Health District Human Research Ethics Committee, Sydney, Australia (reference number HREC/13/SAC/359). The findings will be disseminated in peer-reviewed journals and through professional and scientific conferences.

The trial was registered with the Australia New Zealand Clinical Trials Register (ACTRN12614000936628).

The protocol paper has been published:

[name], [name], [name], [name], [name], [name], [name], [name], [name], [name], [name], [name], [name], [name], [name], [name], [name], [name], [name], [name], [name], [name] (2016). Effect of affordable technology on physical activity levels and mobility outcomes in rehabilitation: protocol for the AMOUNT (Activity and MObility UsiNg Technology) rehabilitation trial. *BMJ Open* 2016; 6:e012074. doi:10.1136/bmjopen-2016-012074.

# **2. DATASET ANALYSED**

The main (intention-to-treat (ITT)) dataset analysed will be constituted of all patients randomised into the study irrespective of adherence to interventions.

#

# **3. STUDY OUTCOMES**

## 3.1 Primary outcomes

The coprimary outcomes will be (1) physical activity (proportion of the day spent upright) and (2) mobility (lower extremity continuous summary performance measure derived from the Short Physical Performance Battery, SPPB) 6 months after randomisation.

1. Physical activity as the proportion of the day spent upright, assessed over a 7-day period using the activPAL activity monitor (PAL Technologies Ltd, Glasgow, UK) at 6 months post randomisation will be the primary outcome. Upright time is calculated as the sum of the time spent stepping and standing. Wear-time authentication was performed on each participant’s data set to determine whether data were to be included in the analysis. Acceptable wear time was set a priori and defined as 4 days, for 24 hours per day. See Appendix 2 for a full description of the validation and data preparation process.
2. Mobility will be lower extremity continuous summary performance score (CSPS)^1^(0–3) of the SPPB.^2^ The SPPB involves measurement of timed ability to stand unsupported (for 10 s) with the feet in three different positions of increasing difficulty (feet together, semitandem and tandem), time taken to walk 4 m and time taken to stand up from a chair and return to a seated position five times. The 6-month CSPS will be the primary outcome measure.

Using the formula to calculate the CSPS^1^, and based on our own baseline data: a score of 0 will be given for participants unable to perform the task for the timed standing balance components (as a low score is a poor score); 11.2 cm/sec for gait (a value corresponding to the 99^th^ percentile [i.e. worst 1% who could perform the task] of baseline performance of individuals completing the task) was assigned to individuals who were physically unable to perform the task or who had a performance below the 99^th^ percentile; 83.0 s (a value corresponding to the 99th percentile of baseline performance of individuals completing the task) was assigned to individuals who were unable to perform the five chair stand or who had a performance above the 99^th^ [i.e. worst 1% who could perform the task] percentile.

In summary, the two primary endpoints will be summarised by:

1. The between-group difference in the proportion of the day spent upright (assessed using the activPAL) at 6 months.
2. The between-group difference in mobility (assessed using the CSPS) at 6 months.

## 3.2 Secondary outcomes

Secondary outcomes will be measures of physical activity and mobility, cognition, self-reported physical activity, activity performance and participation, utility-based quality of life, balance confidence, technology self-efficacy and falls in the 6 months after randomisation. In addition, self-reported measures of technology usability and enjoyment will be obtained from the intervention group.

The endpoints are between-group differences in the following:

**Balance and mobility:**

1. proportion of the day spent upright at 3 weeks (time spent standing and stepping from activPAL)
2. average number of steps per day at 3 weeks and 6 months from activPAL
3. average number of sit to stands per day at 3 weeks and 6 months from activPAL
4. SPPB, at 3 weeks, CSPS (0-3)
5. SPPB, at 3 weeks and 6 months, total score (0-12). The SPPB total score is calculated from three components: the ability to stand for up to 10 seconds with feet positioned in three ways (together side by side, semi-tandem and tandem), time to complete a 3 or 4-metre walk and time to rise from a chair five times.^2^ For the tests of standing balance a score is given depending on the ability to maintain balance in each of these positions. For the other two tests, scores are given firstly on the ability to complete the tasks and secondly the time taken to complete each task. Each task is scored out of 4, with the scores from the 3 tests summed to give a total, with a maximum of 12 and a minimum of 0. A higher score indicates a higher level of function, while lower scores indicate a lower level of function.
6. SPPB, at 3 weeks and 6 months, subscale scores for balance tests, gait speed test and chair stand test (0-4).
7. de Morton Mobility Index (DEMMI) score^3^, at 3 weeks and 6 months. The DEMMI is a 15-item hierarchical measure that covers the mobility spectrum from bed mobility to high-level independent mobility. The DEMMI gives a raw score out of 19 and this is converted into a DEMMI score between 0 to 100 (see appendix 3). A higher score indicates a higher level of mobility.
8. Single leg stance score, at 3 weeks and 6 months. Timed single leg stance (max 10 s).
9. Maximal balance range test at 3 weeks and 6 months, measures the maximum distance participants can lean backward and forward.^4^ The maximum anterior-posterior displacement in mm is the variable used.
10. Step Test at 3 weeks and 6 months, the number of times the participant is able to step one foot on, then off, a 7.5cm block as quickly as possible in 15 seconds.^5^ The average number of steps between the two legs is the variable calculated.

**Activity and participation**, the WHO Disability Assessment Schedule 2.0 (WHODAS 2.0)^6^, a 12-item self-report measure of activity performance and participation covering 6 domains, will be completed at 3 weeks, 12 weeks and 6 months. The scores assigned to each of the 12 items – “none” (1), “mild” (2) “moderate” (3), “severe” (4) and “extreme” (5) – are summed to give a score ranging from 12 to 60, where 12 = no disability and 60 = full disability.

**Physical activity**, the 10-item Incidental and Planned Exercise Questionnaire^7^ assesses the level of physical activity relating to both basic and more demanding activities at 3 weeks, 12 weeks and 6 months. The total time spent doing activities is summed across all components and expressed as hours per week. The score is derived from multiplying frequency score and duration score (see Appendix 4) to create a total duration for the week score: Total activity score = (Q1*Q2) + (Q3*Q4) + (Q5*Q6) + (Q7*Q8) + (Q9*7) + (Q10*7), with a higher score indicating a higher physical activity level. Subscale scores will also be calculated for home exercise (Q2) and walking activity (Q5*Q6)+(Q6*Q7).

**Fall-related confidence** will be assessed with the Activities-Specific Balance Confidence Scale^8^ at 3 weeks, 12weeks and 6 months. This is a 16-item scale with each item scored between 0 to 100 with 0 representing no confidence and 100 representing complete confidence. The 16 items are summed together and then divided by 16 (the number of items) to give a total score between 0 and 100 with a higher score indicating a higher confidence in balance.

**Cognition**, will be assessed using the Trail Making Test parts A and B^9^ at 3 weeks and 6 months. Trails Part A measures processing speed and involves participants connecting consecutive numbers (e.g., 1-2-3). Part B is a measure of executive function of ‘task shifting’ and involves participants connecting alternating letters and numbers (e.g.,1-A-2-B). The difference in time between the two parts (B minus A) will be calculated to isolate the executive component of this test with a lower time reflecting better executive function.^10^ Trails Part A score and Trails Part B scores will also be calculated.

**Health-related quality of life:**

1. European Quality of Life-5 dimensions (EQ-5D-5L)^11^ assessed at 3 weeks 12 weeks and 6 months. The EQ-5D-5L has 5 questions each with 5 levels as well as a VAS score from 0 to 100. A health utility score will be determined from the 5 questions using published scoring algorithms. In addition, the score for each item will be determined and the EQ VAS score (0-100) will be reported.
2. Short Form 6-dimensions questionnaire (SF-6D) calculated from the SF-36^12^ assessed at 3 weeks, 12 weeks and 6 months. The 11 questions are in 6 domains (physical functioning, role participation, social functioning, bodily pain, mental health, and vitality) and using the published Australian scoring algorithm, we will determine the resulting SF-6D utility score.

**Falls** will be assessed over the 6-month period after randomisation. Data will be collected during the inpatient stay using study site incident documentation systems and hospital databases. After discharge, participants will be asked to complete monthly calendars for the remainder of the trial documenting any falls and service usage. Data will be obtained by phone from participants who are unable or unwilling to complete a calendar.

**Technology self-efficacy,** will be measured using the Modified Computer Self-Efficacy Scale^13^ assessed at 3 weeks, 12 weeks and 6 months. This is a 10-item scale, each item scored between 1 (not at all confident) and 10 (completely confident). The total score is the sum of each item score and will be between 10 and 100 (higher score associated with higher levels of confidence). Exposure to common technologies (e.g., smartphone, computer) in the month prior to hospitalisation and during their inpatient and community components of the trial will be measured using a purpose-designed survey.

**Adverse events** (minor and serious) will be monitored throughout the trial. For the purpose of this trial an adverse event is defined as an unwanted and usually harmful outcome (e.g., fall, seizure, cardiac event). The event may or may not be related to the intervention, but it occurs while the person is participating in the intervention, that is, while they are undertaking mobility or physical activities using technology. Adverse events will be categorised as minor AEs (MAEs) or serious AEs (SAEs). A MAE is defined as an incident that occurs while the person is participating in the intervention that results in no injury or minor injury. For example, a fall where the person sustains a small cut or bruise that requires none or minor medical intervention. A SAE is defined as an incident that occurs while the person is participating in the intervention that results in death, serious injury or re-hospitalisation. Examples of SAEs are death, myocardial infarction, serious falls, serious fractures, epilepsy/seizures.

**Deaths** in both groups will be documented.

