## 4.7 Economic evaluation (this will not be reported as part of the main paper)

Health and community service usage data collected from participant-completed calendars, hospital databases and medical records (rehabilitation length of stay, readmissions including type, other settings length of stay e.g. transitional care, number and type of community services at home) will be used to calculate health service utilisation and costs to inform the conduct of an economic evaluation. The cost of the intervention (staff and equipment) will also be calculated from trial records and used in the cost effectiveness analysis. The Incremental Cost-Effectiveness Ratio will be calculated to assess the relative costs and benefits in terms of gain in mobility (the proportion of participants achieving a clinically meaningful improvement on the 12-point SPPB scale) and QALYs.

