## 4.8 Intervention group measures

Adverse events reported in the intervention group, adherence, impression of ‘usability’ and ‘enjoyment’ will be summarised.

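### Adverse events are defined only during technology use, so the control arm is zero by construction; the SAP places them inconsistently and plans no between-arm analysis of readmissions or other serious events

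*SAP*

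**What the plan says.** Four places in the SAP bear on this.

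- **Section 3.2, lead-in.** The list of secondary outcomes opens with "The endpoints are between-group differences in the following". The adverse events paragraph comes later in the same section. The sentence just before the lead-in, which names the secondary outcomes, ends with falls and does not mention adverse events.
- **Section 3.2, Adverse events.** An event need not be related to the intervention, but it counts only if "it occurs while the person is participating in the intervention, that is, while they are undertaking mobility or physical activities using technology". The two grades repeat the limit: "A MAE is defined as an incident that occurs while the person is participating in the intervention that results in no injury or minor injury", and "A SAE is defined as an incident that occurs while the person is participating in the intervention that results in death, serious injury or re-hospitalisation". A separate line says that deaths will be recorded in both groups.
- **Appendix 1.** Adverse events share a row with falls and deaths, collected monthly. That row lies outside the block reserved for measures taken only in the intervention group.
- **Section 4.8, Intervention group measures** (the second of two sections numbered 4.8). The planned analysis is a summary of "Adverse events reported in the intervention group", together with adherence, usability and enjoyment.

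Two further places matter. Fall rates are compared between groups by negative binomial regression (sections 4 and 4.5). Service-use data, including "rehabilitation length of stay, readmissions including type", are collected for the economic evaluation in section 4.7, whose title says it stays out of the main paper.

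**The concern.** The research questions compare technology plus usual care with the same care without it ("compared to usual care alone"). A usual-care participant does not take part in the intervention and so cannot have a minor or serious adverse event as defined, whatever happens to them. Under the section 3.2 lead-in or Appendix 1, a reader would expect a two-arm result. Under the definition and section 4.8, only a one-arm count exists.

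More is at stake than labelling. The definition is neutral on cause but strict on timing. A cardiac event, seizure or readmission that arises after a session is not an adverse event even in the treated arm. The intervention aims to raise physical activity, so readers will ask whether serious events overall rose, fell or stayed the same. A count of events during technology use, with no control rate beside it, cannot answer that.

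**Working it through.** The SAP states no adverse event rate, expected count or sample size, so there is no figure to reproduce. The check is one of definition, with a short illustration.

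**1. Who can contribute.** The definition (section 3.2) requires participation in the intervention using technology. The comparator (section 1) is usual care alone. The control count is therefore 0 by construction.

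**2. What a difference would measure.** Let p1 and p0 be the true 6-month risks of an event in the intervention and control arms. Let f be the share of intervention-arm events that happen during technology use. Assume at most one event per person.

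- Counted risk, intervention arm: p1 × f
- Counted risk, control arm: 0
- Counted difference: p1 × f − 0 = p1 × f
- True difference: p1 − p0

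The counted difference does not involve p0 and can never be negative. A risk ratio would divide by zero.

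Illustration; every value is assumed and none comes from the SAP:

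| p1 | p0 | f | True difference | Counted difference |
|---|---|---|---|---|
| 0.10 | 0.10 | 0.05 | 0 | 0.10 × 0.05 = 0.005 |
| 0.20 | 0.20 | 0.20 | 0 | 0.20 × 0.20 = 0.04 |
| 0.40 | 0.40 | 0.50 | 0 | 0.40 × 0.50 = 0.20 |
| 0.20 | 0.40 | 0.20 | −0.20 | 0.20 × 0.20 = 0.04 |

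With equal true risks the counted difference runs from 0.005 to 0.20 over these ranges. In the last row the intervention halves the true risk, and the count still shows an excess.

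**3. Where the SAP places adverse events.**

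| Place | Implied status |
|---|---|
| Section 3.2 lead-in | Two-arm endpoint |
| Appendix 1 row | Two-arm outcome (outside the intervention-only block) |
| Section 3.2 definition | Intervention arm only |
| Section 4.8, Intervention group measures | Intervention arm only, descriptive |

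Section 3.3 exists for intervention-only measures, and adverse events are not in it.

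**4. What between-arm harm information remains.**

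| Event | Recorded in both arms? | Between-arm analysis planned? |
|---|---|---|
| Falls | Yes, over 6 months | Yes, negative binomial regression |
| Deaths | Yes | None specified |
| Readmissions | Service-use sources, section 4.7 | Only within the economic evaluation |
| Cardiac events, seizures and non-fall injuries outside technology use | Only if they lead to a recorded service contact | None |
| Events during technology use | No, intervention arm only | No, descriptive summary |

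**The case against.** The strongest reply is that no planned analysis fails. The SAP specifies no between-group test, model or ratio for adverse events. The sentence naming the secondary outcomes leaves them out, and the only analysis is an intervention-arm summary, which agrees with the definition. The between-group reading rests on a general lead-in and the position of a row in Appendix 1. This stands. A reader might infer that the trial has a planned safety comparison that is impossible to estimate. The documents do not support that: no comparison is specified, and a difference could be computed but would carry no comparative meaning.

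Second, harm is not unmeasured in the control arm. Falls are counted without the technology limit and compared, and deaths are documented in both groups. A fall hours after a session still enters the falls analysis. This also stands, and it narrows the gap to readmissions and to serious events other than falls and deaths.

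Third, a reader might infer that almost all follow-up time lies outside the definition. The SAP gives no session length. It also does not say whether walking with an activity monitor counts as using technology; if it does, the covered time could be large. Share of clock time is not share of risk either. No such figure should be attached to this point, although the unclear boundary is itself worth settling.

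Fourth, confining adverse events to delivery of the intervention is a recognisable design choice, and the protocol, which may say more on safety, is not shown. That is fair, but it does not reconcile the four places in the SAP or give the count a comparator.

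**Conclusion.** The point holds in a limited form. By the SAP's own definitions, minor and serious adverse events can occur only in the intervention arm. The counts are descriptive and say nothing about the effect of the intervention on harm. The section 3.2 lead-in and Appendix 1 conflict with the definition and with section 4.8. Beyond falls, which are compared, and deaths, which are documented without a stated analysis, no between-arm safety analysis covers readmissions or other serious events outside technology use.

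The control count of 0 follows from the text and needs no assumption. How many events the rule leaves out cannot be derived from the SAP, and the illustrative differences of 0.005 to 0.20 depend wholly on assumed risks and shares. The co-primary analyses are untouched. Safety reporting would be incomplete, and this should be put right because much of the needed information is already being collected.

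**What to change.** **Reconcile the text.** Move adverse events to section 3.3, or label them in section 3.2 as a descriptive intervention-arm measure outside the between-group list. Split the Appendix 1 row so that falls and deaths stay two-arm and adverse events go into the intervention-only block. Keep the intervention-arm summary in section 4.8, state there that the count is not comparative, and say what qualifies as using technology.

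**Add one by-arm table.** Report deaths and readmissions from randomisation to 6 months, plus hospital-recorded serious injuries where existing records identify them. For each, give by arm the number of participants with at least one event and the event count, with a rate ratio and 95% CI. The negative binomial model already planned for falls can serve for repeated events, with time at risk as an offset. The sources are the incident systems, hospital databases and monthly calendars described for falls in section 3.2, and the hospital databases and medical records named in section 4.7.

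**Cost.** Changes of wording, one table, and some coding of readmission type blind to allocation. The rate ratio will probably be imprecise and should be presented as estimation rather than a test. Non-fall injuries that led to no service contact will be missed in both arms, and section 4.7 does not say that readmission type means cause, so the injury line may be incomplete. The table should say so.
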